**Items for random prompts**					
	Positive and negative affect [70]	“Since the last EMA^a^ signal, how much of the time did you feel...?” Cheerful In good spirits Extremely happy Calm and peaceful Satisfied Full of life So sad Nervous Restless or fidgety Hopeless Worthless Everything was an effort		Very slightly or not at all A little Moderately Quite a bit Extremely	
	Perceived stress scale [49]	“How certain do you feel that you can deal with all the things that you have to do right now?”		Not at all A little Quite a bit Extremely	
	Perceived stress scale [49]	“How confident do you feel about your ability to handle all of the demands on you right now?”		Not at all A little Quite a bit Extremely	
	Daily hassles [71]	“Have you experienced a stressful event since your last entry?”		Yes or no	
	Daily hassles [71]	“Have you experienced a stressful or problematic social interaction since last entry?”		Yes or no	

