We will use a smartphone app to record EMA data via a mobile phone; these methods have been previously used for adults [36,37]. We will use two approaches for participants to record their PA, neighborhood environment, and stress. The first is an event contingency assessment. With this assessment, participants will be expected to record within the smartphone app when they engage in a certain behavior (eg, PA) within 15 minutes of the event occurring. The other type of assessment involves random survey prompts. Participants will respond to a series of questions on each day of the week. They will receive EMA random prompts for each assessment for that day (up to three random prompts for each assessment [morning, afternoon, and evening] and a maximum of nine prompts each day). The survey may take approximately 2-3 minutes to complete each time. Each item assesses the type of neighborhood context for the physical environment (eg, home, work, and outdoor), vegetation (amount of trees), traffic (amount of traffic), and safety (feeling safe and violence). Mood (positive and negative affect) and stressors (eg, daily hassles) from the EMA survey will be used specifically as psychosocial factors for each sub-aim. Previously validated EMA surveys and protocols for adults will be used in the proposed study [36,37].

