**Figure 5 figure5:**
[figure not shown]
GPS activity space buffers based on individuals’ daily paths.

In Table 3, real-time EMA measures will include perceived neighborhood social environment (eg, violence and safety), mood states (positive or negative affect [70]), perceived stress (eg, stressed and irritated [49]), and daily hassles (eg, work load [71]) with three random prompts within defined timeframes (7-9 AM, 11 AM-1 PM, and 5-7 PM) throughout the day (Table 3; Figure 6) [36]. Participants will initiate their own EMA recording when they start engaging in a certain activity (ie, event contingency; Table 3; Figure 6) [68,69]. The event contingency approach is based on a self-initiated response to behaviors and contexts. Participants will be instructed on how to initiate the EMA recording and respond to a certain activity and when to initiate their EMA recording. For example, when participants commute to work by car, they initiate it by themselves and record their mode of activity in the smartphone app. EMA measures will be merged with GPS activity space measures with the respective timestamps. Before the full pilot study, we tested GPS units and EMA using a smartphone app (ilumivu, Inc) to identify any potential barriers to use.

**Table 3 table3:** Random prompts and event contingency items for ecological momentary assessment.

Variable			Item		Response options

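### The EMA daily-hassles items look back to the last entry, so the hassles score used as a moderator in sub-aims 1 and 2 varies with prompt compliance as well as with stressors

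*Protocol article*

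**What the plan says.** Table 3 of the protocol article lists the random-prompt items and uses three different time frames:

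- **Daily hassles** (two yes/no items): "Have you experienced a stressful event since your last entry" and "Have you experienced a stressful or problematic social interaction since last entry". The window starts at the participant's own last entry.
- **Affect:** the stem refers to the last EMA "signal, how much of the time did you feel". The window starts at the last signal, whether or not it was answered.
- **Perceived stress:** for example "How confident do you feel about your ability to handle all of the demands on you right now". There is no look-back.

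Under Exposures, the EMA text describes measures collected "with three random prompts within defined timeframes (7-9 AM, 11 AM-1 PM, and 5-7 PM". The same app takes event-contingent records: "Participants will initiate their own EMA recording when they start engaging in a certain activity". The event-contingency items in Table 3 cover activity, place, vegetation, traffic, litter and safety. None asks about hassles. The term 'entry' is not defined anywhere in the article.

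On use, the Devices section says: "Mood (positive and negative affect) and stressors (eg, daily hassles) from the EMA survey will be used specifically as psychosocial factors for each sub-aim". Table 2 lists daily hassles among the moderators. The Limitations section states that the analyses are at the person level.

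**The concern.** A yes/no item with an open look-back is more likely to be answered yes when the window is longer. Here the length is set by the participant's own response pattern. Two women with the same true stressor rate but different compliance will have different expected hassles scores. In a person-level analysis, that difference goes straight into the moderator.

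A second path depends on how 'entry' is read. If a self-initiated activity recording counts, it restarts the hassles clock without asking about hassles. Stressors between the previous entry and that recording are then never captured. Women who log more activity would score lower on hassles at equal stress. Physical activity is itself a covariate and the other moderator, so this would build in an artificial inverse link between hassles and activity logging.

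**Working it through.** The article states no figure for the hassles score, so there is none to reproduce. The check asks how far the score moves when the true stressor rate is held constant.

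**Inputs from the article:** three prompts a day, in the bands 7-9 AM, 11 AM-1 PM and 5-7 PM; 14 days; yes/no items.

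**Assumptions (not in the article):** a 16-hour waking day from 7 AM to 11 PM; stressors arriving at random at a constant rate λ = 1/8 per waking hour (2 per day), the same for every woman; prompts missed at random; activity recordings, where they count, at random times.

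**Window lengths.** With prompts at the band midpoints, the waking gaps are 4, 6 and 6 hours (the last is 5 hours to 11 PM plus 1 hour the next morning). The mean is 16/3 = 5.3 hours. At compliance c the mean look-back is 16/(3c): 6.7 hours at 80% and 10.7 hours at 50%.

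**Share of yes.** P(yes | window W) = 1 − exp(−λW). The chance of no stressor is exp(−4/8) = 0.607 over a 4-hour gap and exp(−6/8) = 0.472 over a 6-hour gap. Averaged over the starting position, the chance of no stressor is:

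- over one gap: (0.607 + 2 × 0.472)/3 = 0.517
- over two gaps: (2 × 0.607 × 0.472 + 0.472²)/3 = 0.265
- over three gaps: 0.607 × 0.472² = 0.135, after which the pattern repeats multiplied by 0.135.

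The look-back spans k gaps with probability c(1 − c)^(k−1). Hence:

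- c = 1: 1 − 0.517 = 48%
- c = 0.8: 1 − (0.8 × 0.517 + 0.16 × 0.265 + 0.032 × 0.135 + …) = 54%
- c = 0.5: 1 − (0.5 × 0.517 + 0.25 × 0.265 + 0.125 × 0.135 + …) = 65%

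Simulation over 14 days, with prompt times random within each band, gave 47%, 53% and 64%, within about one point of the closed form.

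**Count of yes per day** = 3 × c × share: 3 × 0.483 = 1.45 at full compliance and 1.5 × 0.652 = 0.98 at 50%. The simulated values were about 1.4 and 0.95. The count moves in the opposite direction to the share.

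**Other stressor rates (simulated, compliance from 100% to 40%).** At 1 per day the share goes from 28% to 49%; at 2 per day from 47% to 70%; at 3 per day from 63% to 80%. At 60% compliance a woman with 2 stressors a day scores 61%, close to the 63% of a fully compliant woman with 3 a day.

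**If activity recordings count as entries (full compliance).** With recordings at rate μ per waking hour and a gap L since the previous prompt, P(yes) = λ/(λ + μ) × (1 − exp(−(λ + μ)L)). For two recordings a day, μ = 1/8:

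- L = 4: 0.5 × (1 − exp(−1)) = 0.316
- L = 6: 0.5 × (1 − exp(−1.5)) = 0.388
- average: (0.316 + 2 × 0.388)/3 = 36%, against 48% without recordings (simulated: 36% against 47%).

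If only answered prompts count as entries, this effect is zero and the missed-prompt effect remains (simulated: 49% at full compliance to 70% at 40%).

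**Signal anchor.** With the window starting at the last signal, the simulated share was 47.5%, 47.9%, 48.3% and 47.9% at 100%, 80%, 60% and 40% compliance. A raw count would still fall, from 1.39 to 0.56 per day.

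**The case against.** The strongest reply has five parts.

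1. **The meaning of 'entry'.** The hassles items sit under the random-prompt heading, and self-initiated logs are called recordings. 'Last entry' may simply mean the last answered survey. This stands. A reader might infer that active women will appear less stressed, but the article supports that only on one reading of an undefined word.

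2. **Scoring.** The article gives no scoring rule, and this is normally left to a fuller document. A reader might infer that poor responders will look more stressed. That is true of a proportion and false of a count, so no direction can be claimed. The defect is in the printed item wording, however, and neither simple score escapes it.

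3. **Scope.** Only the two hassles items are affected. Reading this as a flaw in the stress moderators generally is not supported: the EMA perceived-stress items have no look-back, the affect items use the signal, and the Statistical Analysis section's example for the split at the mean is the perceived stress scale score.

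4. **Compliance plans.** The Compliance section plans daily follow-up, monitoring of missingness and latency, and an exploratory pattern-mixture analysis. These may reduce missed prompts. They do not correct the look-back length of prompts that were answered.

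5. **Source wording and consequence.** The items cite a source, and the article says previously validated surveys are used, so changing the wording has some cost. Moderation is tested only after a significant exposure is found, in a pilot. Both points limit the weight of the concern. Neither makes the windows comparable between women.

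The article also gives no evidence that compliance or logging differs by ward, so a ward-related distortion cannot be asserted.

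**Conclusion.** The point holds for the two daily-hassles items. As worded, their look-back stretches with missed prompts, so the person-level hassles score depends on compliance at equal true stress. At the assumed 2 stressors per waking day and three prompts a day, the share of yes rises by about 6 points at 80% compliance and 17 points at 50%, while a count falls by about a third (1.4 to 0.95 per day). These sizes rest on assumed stressor rates and compliance, and on the three-prompt schedule; the Devices section allows up to nine prompts a day. The mechanism itself rests only on the wording.

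The activity-logging effect (47% to about 36% with two recordings a day) is conditional on 'entry' including self-initiated recordings. This is an inexpensive improvement to one moderator. It does not bear on the ward comparisons or on the other EMA measures.

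**What to change.** **Preferred.** Anchor both hassles items to the last scheduled EMA signal, as the affect items already are, or to a fixed number of hours before the prompt. State that self-initiated recordings do not reset the window. Score hassles as the proportion of answered prompts with a yes, not as a count.

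**If the cited wording must stay.** Tell participants that 'entry' means the last answered random prompt, and use the app timestamps to account for look-back time. Dividing the number of yes answers by hours covered is not enough, because one yes can stand for several events. With all waking hours covered it only rescales the count: 1.45/16 = 0.091 per hour at full compliance and 0.98/16 = 0.061 at 50%, against a true 0.125. The rate per waking hour should instead be estimated from P(yes) = 1 − exp(−rate × hours), that is, a complementary log-log model with log hours as offset.

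**Cost.** A text change in the app with a slight departure from the cited item wording, or one instruction and one derived variable from timestamps that the plan already uses for merging. Neither route deals with prompts missed because of stress itself; that remains a matter for the planned missingness analysis.

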**Items for event contingency** **[68,69]**					
	Physical activity behavior	“What type of physical activity/exercise are you doing?”		Walking Running or jogging Weightlifting or strength training Using cardiovascular equipment Bicycling Other (write in)	
	Physical context	“WHERE are you?”		Home (indoors) Home (outdoor) Work (indoor) Outdoors (not at home) Car, van, or truck Other (write in)	
	Physical context	“WHERE are you AT HOME?” (Indoors)		Bedroom Family or living room Kitchen Garage Other (write in)	
	Physical context	“WHERE are you AT HOME?” (Outdoors)		Pool Deck, patio, or balcony Yard Driveway Other (write in)	
	Physical context	“Where are you OUTDOORS?” (Outdoors not at home)		Park or trail Road Sidewalk Parking lot Other (write in)	
	Vegetation	“How many TREES AND PLANTS are there in the area where you are right now?”		No trees or plants A few trees and plants Some trees and plants A lot of trees and plants	
	Traffic	“How much TRAFFIC is on the closest street to where you are right now?”		No traffic A little traffic Some traffic A lot of traffic	
	Litter	“How much LITTER or GARBAGE is on the ground where you are right now?”		No litter A little litter Some litter A lot of litter	
	Safety	“Do you feel safe in your current location?”		Yes or no	
	Safety	“Is violence a problem in your current location?”		Yes or no	

^a^EMA: ecological momentary assessment.

**Figure 6 figure6:**
[figure not shown]
Selected random prompts ecological momentary assessment and event contingency ecological momentary assessment. EMA: ecological momentary assessment.

### Merging Multiple Data

Complete master data will be created based on multiple data sources, including PA via accelerometers (ie, 1-minute epochs), GPS units (1-minute epochs), and EMA via a smartphone app (3 times/day). First, each recording of the GPS points will be linked to the respective time-stamped accelerometer data for each minute. Then, EMA data (three times through morning, afternoon, and evening assessments) will be linked to the corresponding GPS and accelerometer data. The complete data will then be collapsed by hours, time of day (morning, afternoon, and evening), and days.

### Statistical Analysis

To test aim 1 hypothesis, we will first test the differences in stress-related neural activity by Wards 3 and 5. Subsequently, we will examine associations between each neighborhood social environment variable based on residential and GPS-derived measures as well as EMA measures separately and stress-related neural activity, adjusting for all covariates. Covariates will include sociodemographic variables (eg, age, race [White or Black adults], and individual-level income) and health-related variables (eg, PA). Each model will be assessed based on the value of the Akaike information criterion (AIC) to select the most parsimonious model. Third (sub-aim 1), after determining a statistically significant neighborhood exposure variable, we will test for an interaction between the specific neighborhood exposure variable and objectively measured PA and psychosocial factors (a potential moderator). If the interaction term is significant, we will stratify the association by high or low objectively measured PA based on the mean and by high or low psychosocial factors (eg, perceived stress scale scores) based on the mean.

To test aim 2 hypothesis, we will first test the differences in the measures of vascular inflammation and function (Table 2) by Wards 3 and 5. Second, we will examine associations between each neighborhood social environment variable based on residential and GPS-derived measures as well as EMA separately and each vascular measure, adjusting for all covariates. The same covariates will be used as in aim 1. Each model will be assessed based on the value of the AIC to select the best-fit model. Third (sub-aim 2), after we identify a statistically significant exposure variable, we will test for an interaction between the specific exposure variable and objectively measured PA and psychosocial factors. If the interaction term is significant, we will then stratify the association by high or low objectively measured PA based on the mean and by high or low psychosocial factors (eg, perceived stress scale scores) based on the mean.

To test aim 3 hypothesis, we will first test the differences in immune cell activation, immune cell function, and biomarker-based immune activation (Table 2) by Wards 3 and 5. Second, we will examine associations between each neighborhood social environment variable based on residential and GPS-derived measures as well as EMA separately and the measures of immune system activation, adjusting for all covariates. The covariates are described in aim 1. Each generalized linear mixed model will be assessed based on the value of the AIC to select the best-fit model.

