Although the neighborhood social environment is an important factor in promoting PA [13], a key limitation in neighborhood social environment research is that the majority of such research systematically focuses on residential areas (ie, home) when investigating relationships between objectively measured environmental exposures via geographic information system (GIS) and PA [13]. However, individuals are generally mobile and engage in daily activities that are not restricted to places close to residential areas (eg, workplace) [14]. This generates a geospatial mismatch between exposures to the neighborhood social environment and locations where health behaviors occur [13,15,16]. Previous studies have also used self-reported PA, resulting in potential recall and social desirability bias [17].

When coupled with the neighborhood social environment as a source of stressors, psychosocial factors, such as chronic stress and depression, have an inverse relationship with PA and ultimately CVD [18]. Furthermore, a recent study in adults without CVD and our research in African American women in Washington, DC, demonstrated that amygdala activity (ie, chronic stress–related neural activity) assessed via 18-fluorodeoxyglucose (FDG) positron emission tomography-computed tomography (PET/CT) were significantly associated with subsequent CVD events [19] and vascular inflammation, a subclinical marker of atherosclerosis [20,21]. In addition, another recent study showed that neighborhood-level socioeconomic status (SES) was inversely associated with amygdala activity and arterial inflammation [22]. These findings are important for validating the relationship between chronic stress because of neighborhood factors and CVD events. However, the major limitations of the previous study were that they did not account for individual-level SES in the analytic models. Instead, they used neighborhood-level SES as a proxy for individual-level SES and examined the associations between neighborhood SES and amygdala activity. Furthermore, participants were chosen from a clinical database, which was not representative of the general US adults, and they were predominantly White adults [22]. Further research is needed to elucidate the associations between psychosocial factors, amygdala activity, and biological markers of adverse cardiac events in diverse populations and to assess both individual- and neighborhood-level SES.

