### Study Participants

A sample of women (at least n=30; 15 White women and 15 African American women) will be recruited from higher SES census tracts within a 15% range of the median household income in Ward 3 (median household income=US $126,184) [30]. The other participants (at least n=30; 15 White women and 15 African American women) will be recruited from lower SES census tracts within a 15% range of the median household income in Ward 5 (median household income=US $68,375) [31]. Participants from Wards 3 and 5 will be matched based on age, race, and BMI.

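### The opening Ward 3 versus Ward 5 comparison in each aim is stated without adjustment: read alone it mixes personal with neighborhood SES, and a plain two-group test would forgo some of the precision that matching offers

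*Protocol article*

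**What the plan says.** The Statistical Analysis section uses the same sequence for all three aims. The opening step is a ward comparison:

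- Aim 1: "we will first test the differences in stress-related neural activity by Wards 3 and 5".
- Aim 2: "we will first test the differences in the measures of vascular inflammation and function (Table 2) by Wards 3 and 5".
- Aim 3: "we will first test the differences in immune cell activation, immune cell function, and biomarker-based immune activation (Table 2) by Wards 3 and 5".

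The second step fits a model for each residential, GPS-derived and EMA exposure. Only here does adjustment appear; for aim 1 the wording is "as well as EMA measures separately and stress-related neural activity, adjusting for all covariates". The covariates are described so: "Covariates will include sociodemographic variables (eg, age, race [White or Black adults], and individual-level income) and health-related variables (eg, PA". Aims 2 and 3 reuse them.

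On design, the Study Participants section states: "Participants from Wards 3 and 5 will be matched based on age, race, and BMI". Race is also balanced by quota within each ward (for Ward 3, "at least n=30; 15 White women and 15 African American women) will be recruited from higher SES census tracts"). The article does not say whether matching is by individual pair or by frequency, and income is not among the matching factors. Tracts are chosen around ward median household incomes of US $126,184 (Ward 3) and US $68,375 (Ward 5).

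The Background section says of an earlier study that "the major limitations of the previous study were that they did not account for individual-level SES in the analytic models".

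**The concern.** Two things follow if the opening step is carried out as it reads.

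The first is confounding. The wards were picked because their incomes differ. A woman in the Ward 3 sample will probably have a higher personal income than her counterpart in Ward 5, and matching does nothing about that. An unadjusted ward difference cannot separate where she lives from what she earns.

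The second is precision. Balancing the wards on age, race and BMI reduces the true sampling variance of the ward difference to the extent that these factors predict the outcome. A plain two-group test does not credit that reduction.

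The contrast will be used. The Expectations section presents Ward 3 versus Ward 5 as what aims 2 and 3 will compare, and the Sample Size Calculation section says that differences in biological measures will feed power calculations for a larger study. A ward difference that partly reflects personal income would be carried into that planning.

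**Working it through.** **The plan's own precision figure.** The only one is the 20% upper bound on the amygdala SD at n = 30. The chi-squared form gives √(29 / 19.768) = 1.211, and a large-sample normal form gives 1 / (1 − 1.2816/√58) = 1.202. The stated 20% reproduces. It concerns an SD, not the ward difference; the article gives no effect size, power or explained variance for the ward comparison.

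**Income.** The documents give the two ward medians: 126,184 / 68,375 = 1.85, and ln(1.85) = 0.613. Three further inputs are assumptions: the ward medians stand in for participants' incomes; the within-ward SD of log income is 0.5 to 0.9; and the outcome changes by b = 0.1 to 0.3 SD per SD of log income.

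- Ward gap in income SDs, d = 0.613 / SD: from 0.613/0.9 = 0.68 to 0.613/0.5 = 1.23.
- Bias in the unadjusted ward difference, b × d: from 0.1 × 0.68 = 0.07 to 0.3 × 1.23 = 0.37 outcome SD.
- SE of the difference at 30 per ward with outcome SD 1: √(2/30) = 0.258. With no ward effect net of income, a nominal two-sided 5% test would then reject in about 6% to 30% of studies.
- Cost of adjusting: the SE is multiplied by √(1 + d²/4), which is √1.116 = 1.056 at d = 0.68 and √1.375 = 1.173 at d = 1.23. That is roughly 6% to 17%, before any gain from outcome variance that income explains.

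**Matching factors.** Let R² be the share of outcome variance explained by age, race and BMI, with the wards well balanced on them. A plain two-group interval is wider than the adjusted one by a factor of about 1/√(1 − R²). The type I error and power columns come from a simulation of 30 exactly matched pairs, 40,000 runs per row, in which the within-pair correlation plays the part of R². Power is for an assumed 0.6 SD difference, plain test against an analysis that uses the matching.

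| Assumed R² | Interval ratio | Type I error, plain test | Power, plain vs matched |
|---|---|---|---|
| 0.1 | 1/√0.9 = 1.054 | 3.9% | 63% vs 66% |
| 0.2 | 1/√0.8 = 1.118 | 2.9% | 64% vs 71% |
| 0.3 | 1/√0.7 = 1.195 | 2.0% | 65% vs 77% |

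**Both together.** At R² = 0.2, adjusting for the matching factors multiplies the SE by √0.8 = 0.894. Adding income brings it to between 0.894 × 1.056 = 0.94 and 0.894 × 1.173 = 1.05 of the unadjusted SE. This treats the two factors as simply multiplying. On these assumptions the income-adjusted contrast is about as precise as the unadjusted one, and it no longer carries personal income.

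**The case against.** The strongest reply is that the article does not name the form of the ward test. It never says that the test is unpaired, that covariates are excluded or that matching will be disregarded, and a condensed article may leave that to the full protocol or SAP. This stands as regards precision: a reader might infer that the matching is ignored and the intervals are too wide, but that is an inference from silence. It stands less well for adjustment, because the article does specify adjustment and in all three aims attaches it to the second step only.

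A reader might also infer that the plan as a whole repeats the fault it finds in the earlier study. It does not. The association models of every aim include individual-level income, and their exposures include residential neighborhood deprivation.

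Nor is the ward contrast the headline of all three aims. In Expectations, the aim 1 paragraph speaks of neighborhood features and amygdala activity, not of wards, and the moderation tests are triggered by a significant exposure variable, not by the ward result.

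BMI is not shown to be left out. The covariate lists are introduced as examples, and the Strengths section says that the study accounts for age, race and BMI. Naming it would settle the matter.

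Finally, a low R² is plausible, since eligibility limits age to 19–45 and BMI to below 30 in healthy women. The study is a pilot sized to estimate an SD, and 30 per ward is a minimum. An argument that dropout would break many matched pairs also fails for the main outcomes: in Table 1, PET/CT, pulse wave velocity and the first blood draw all precede the monitoring period. These points limit the size of the concern but do not answer the one about income.

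**Conclusion.** The concern holds in a limited form. As written, the opening ward comparison in each aim carries neither the matching factors nor individual income. Since income is unmatched and the ward medians differ 1.85-fold, that contrast taken alone cannot be read as a neighborhood association. Under the stated assumptions the distortion is 0.07 to 0.37 SD. The second-step models already deal with it for the exposure analyses.

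The precision loss is conditional. It needs a plain two-group test and matching factors that predict the outcome; it is about 5%, 12% and 20% of interval width at assumed R² of 0.1, 0.2 and 0.3, and it errs on the conservative side. The R², the income SD, the slope and the 0.6 SD difference are all assumptions. The documents do not establish that the intervals will be too wide. This is a cheap improvement to the analysis, not an error that must be corrected before the study can proceed.

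**What to change.** - For each outcome, estimate the ward difference from a regression on ward plus age, race and BMI. This works whether matching is individual or by frequency, and it keeps women without a matched partner.
- Report that estimate with and without individual-level income. Label the version without income as descriptive, and base any statement about neighborhood on the income-adjusted version.
- Name BMI explicitly among the covariates for aims 1 to 3.

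The cost is a few sentences of analysis text; the plan already provides for every variable. The drawback is the SE increase of roughly 6% to 17% from adding income, which is why both estimates should be shown.
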